#### **4.1.2 Systemic adverse events**

Temperature will be measured by the oral route prior to immunisation and one hour later by study personnel, and graded according to appendix 4. Participants will be given digital thermometers to record their temperature in the diary card on the evening of immunisation, and daily thereafter for 7 days, and if still raised, they will be advised to continue to monitor their temperature daily until it returns to normal. The temperature observed by the clinical team will be recorded on the case record forms for visits.

Chills, headache, nausea, vomiting, malaise and myalgia will be graded by the participants according to appendix 4, recorded in the diary card on the evening following immunisation and daily for 7 days, or until resolution of symptoms whichever is longer. On days where a visit coincides with the diary card, the clinical staff will collect the information directly and record it on the case record form, and this will take precedence over diary card entries in the analysis.

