## 1.5 End-points

### 1.5.1 Primary

The primary endpoints are immunogenicity and safety as defined below.

The primary immunogenicity parameter will be the presence of CD8/CD4+ T cell responses defined according to internationally agreed criteria for evaluation of IFN $\gamma$  ELISPOT assays (see section 8),

- in response to *env plus* at least one of the *gag, pol, nef* peptide pools
- at weeks 26 or 28

The primary safety parameters will be graded according to appendix 4, and are:

- Grade 3 or above local adverse event (pain, cutaneous reactions including induration)
- Grade 3 or above systemic adverse event (temperature, chills, headache, nausea, vomiting, malaise, and myalgia)
- Grade 3 or above other clinical or laboratory adverse event confirmed at examination or on repeat testing respectively.
- Any event attributable to vaccine leading to discontinuation of the immunisation regimen.

Note of clarification 8th Nov 2006: This will capture all Serious Adverse Events (SAE) as defined by ICH GCP as well as other grade 3 and 4 events that do not meet the criteria of an ICH GCP SAE.

Data on local and systemic events listed above will be solicited with specific questions or using a diary card for a minimum of 7 days following each immunisation. Data on other clinical events and laboratory events will be collected with an open question at each visit and through routine scheduled investigations respectively.

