### **Appendix 3 Packaging and labelling**

To be added when finalised

**Appendix 4 Grading of clinical and laboratory adverse events****Based on systems in use at the MRC CTU, IAVI and NIH Division of AIDS**

|                |                |                            |     |                       |
|----------------|----------------|----------------------------|-----|-----------------------|
| Abbreviations: | ULN            | Upper Limit of Normal      | LLN | Lower Limit of Normal |
|                | R x | Therapy                    | Req | Required              |
|                | Mod            | Moderate                   | IV  | Intravenous           |
|                | ADL            | Activities of Daily Living | Dec | Decreased             |

For events not specified in the tables below the following grading should be applied:

|                    |                                                                                                                                             |
|--------------------|---------------------------------------------------------------------------------------------------------------------------------------------|
| Grade 1 (mild)     | No medical intervention required and/or minimal effect on daily activities such that slightly reduced for no more than 48hrs                |
| Grade 2 (moderate) | Repeated medication or medical intervention required and/or activity reduced up to half usual level for more than 48 hrs                    |
| Grade 3 (severe)   | Extensive/prolonged medical intervention or repeated prescribed medication; bed rest or activity reduced by >50% of usual level; can't work |
| Grade 4 (extreme)  | Hospitalisation and/or life-threatening                                                                                                     |

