| Malaise                                         | Transient,easily tolerated and/or normal activity reduced                                                                          | Fatigue such that spends ½ day in bed ≤ 2d                                                                                                                                                                                                        | Fatigue such that in bed all day or in bed ½ day >2d                                                                                                                                                          | Hospitalisation                                                                                         |
| Chills / rigors                                 | Requiring symptomatic treatment                                                                                                    | Prolonged >6hrs requiring regular analgesics for mild-moderate pain or Occasional analgesics for moderate-severe pain                                                                                                                             | Repeated analgesics for moderate-severe pain                                                                                                                                                                  | Rigors                                                                                                  |

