### Appendix 5 Diary Card

#### Guide for grade of general reaction

|                                        | Grade 1
mild                                                       | Grade 2
moderate                                                     | Grade 3
severe                                             | Grade 4
Extreme |
|----------------------------------------|-------------------------------------------------------------------------------|---------------------------------------------------------------------------------|-----------------------------------------------------------------------|----------------------------|
| Chills/rigors                   | Mild hot/cold flush requires blanket or occasional aspirin/paracetamol | Limiting daily activity >6 hours, or need regular aspirin/paracetamol | Uncontrollable shaking, treatment from doctor needed           | Hospitalisation     |
| Malaise/abnormal tiredness      | Normal activity reduced – not bad enough to go to bed                  | Fatigue such that ½ day in bed for 1 or 2 days                           | Fatigue such that in bed all day or ½ day for more than 2 days | Hospitalisation     |
| General (all over) muscle aches | No limitation of activity                                              | Muscle tenderness, limited activity e.g. difficulty climbing stairs      | Severe limitation e.g. can't climb stairs                      | Hospitalisation     |
| Headache                        | No treatment or responds to paracetamol like treatment                 | Regular paracetamol like treatment needed                                | Regular strong painkillers treatment needed                    | Hospitalisation     |
| Nausea                          | Intake maintained                                                      | Intake reduced less than 3 days                                          | Minimal intake 3 days or more                                  | Hospitalisation     |

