| Vomiting                        | Less than 4 x a day or lasting less than 1 week                        | At least 4 x day or lasting 1 week or more                               | Unable to keep any food or fluids down                         | Hospitalisation     |

- Complete at approximately the same time every day ONLY on days that you are NOT going to clinic
- Fill in temperature and record the grade of other general reactions (use the table above as a guide)
- Add any comments regarding other symptoms
- Record any medication taken including over the counter medicines and anything taken to relieve local reactions
- Record the grade, or size in cm, of local reactions overleaf
- Please contact a member of the trials staff as soon as possible if you experience any symptoms of grade 3 or 4
- When the diary card is complete, please return it to a member of trials staff at your next visit

|                                                               | 12 hrs      | Day 1       | Day 2       | Day 3       | Day 4       | Day 5       | Day 6       | Day 7       |
|---------------------------------------------------------------|-------------|-------------|-------------|-------------|-------------|-------------|-------------|-------------|
| General Symptoms                                       |             |             |             |             |             |             |             |             |
| Date                                                   |             |             |             |             |             |             |             |             |
| Temperature °C                                         |             |             |             |             |             |             |             |             |
| Chills/rigors                                          |             |             |             |             |             |             |             |             |
| Malaise/ tiredness                                     |             |             |             |             |             |             |             |             |
| General muscle aches                                   |             |             |             |             |             |             |             |             |

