**Guide for grade of local reactions**

|                                                                        | Grade 1
mild                                       | Grade 2
moderate                      | Grade 3
severe                | Grade 4
Extreme |
|------------------------------------------------------------------------|---------------------------------------------------------------|--------------------------------------------------|------------------------------------------|----------------------------|
| Pain in injected muscle (including ache) NOT discomfort in skin | No treatment or responds to paracetamol like treatment | Regular paracetamol like treatment needed | Regular strong painkillers needed | Hospitalisation     |
| Itching or irritation in the skin at the site of injection      | No treatment or responds to paracetamol like treatment | Regular paracetamol like treatment needed | Regular strong painkillers needed | Hospitalisation     |

| Local Symptoms – please put in grade, including 0 if no symptoms and measure maximum width of skin lesion in cm |        |       |       |       |       |       |       |       |       |       |       |       |       |       |       |       |
|------------------------------------------------------------------------------------------------------------------------|--------|-------|-------|-------|-------|-------|-------|-------|-------|-------|-------|-------|-------|-------|-------|-------|
|                                                                                                                        | 12 hrs |       | Day 1 |       | Day 2 |       | Day 3 |       | Day 4 |       | Day 5 |       | Day 6 |       | Day 7 |       |
|                                                                                                                        | left   | right | left  | right | left  | right | left  | right | left  | right | left  | right | left  | right | left  | right |
| Pain at injection site                                                                                          |        |       |       |       |       |       |       |       |       |       |       |       |       |       |       |       |

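### For nausea, vomiting and chills, the diary card sets grade 3 differently from Appendix 4, the scale the protocol names for the primary safety endpoint

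*Protocol*

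**What the plan says.** Protocol Section 1.5.1 fixes the scale: "The primary safety parameters will be graded according to appendix 4". The systemic part of that endpoint is any grade 3 or higher event among seven items: temperature, chills, headache, nausea, vomiting, malaise and myalgia.

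Section 4.1.2 says who grades and how: "Chills, headache, nausea, vomiting, malaise and myalgia will be graded by the participants according to appendix 4". Entries are made in the diary card. On days when a visit coincides, staff collect the information directly and their record takes precedence in the analysis. The card itself is to be completed only on non-clinic days.

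Appendix 4 opens with a general rule for events that have no row of their own. Its grade 3 covers extensive or prolonged intervention, repeated prescribed medication, inability to work, and "bed rest or activity reduced by >50% of usual level". There is a row for "Chills / rigors" but none for nausea or vomiting.

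Appendix 5 gives participants a separate table and tells them to use it as a guide. Grade 3 nausea is "Minimal intake 3 days or more". Vomiting is grade 2 when it is "At least 4 x day or lasting 1 week or more", and becomes grade 3 only when nothing eaten or drunk stays down. Grade 3 chills/rigors is "Uncontrollable shaking, treatment from doctor needed".

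Section 8.2 says that the Clinical Investigators grade all safety endpoints and the Operational Sub-Group reviews them. Unresolved queries about grade go to the Trial Coordinating Committee. The two groups are then compared by Fisher's exact test on proportions.

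**The concern.** The protocol tells participants to grade on one scale and gives them another. This would matter little if the two agreed at grade 3, since that is where the primary safety endpoint is cut. For three named components they do not. A participant could then be counted or not counted according to which table was applied. Both sources feed the same proportion: the diary on most solicited days, and the clinic record on visit days. Section 7.7.2 also uses grade 3 or 4 events attributed to a product as the basis for a pause, so the meaning of grade 3 is not only an analysis detail.

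**Working it through.** There is no planned figure to reproduce. The check sets the two scales side by side at the endpoint threshold.

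| Component | Appendix 4, grade 3 | Diary card, grade 3 | Agree at grade 3? |
|---|---|---|---|
| Nausea | General rule: intervention, bed rest, activity or work | Intake and duration | No |
| Vomiting | General rule, as above | Nothing stays down | No |
| Chills/rigors | Repeated use of stronger painkillers | Shaking and a doctor's treatment | No |
| Headache | Repeated stronger painkillers, or intractable | Regular strong painkillers | In substance |
| Malaise | All day in bed, or half-days beyond two days | Same | Yes |
| Myalgia | Severe limitation | Same | In substance |
| Temperature | Measured value | Measured value | Not affected by wording |

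Three of the seven components therefore differ. Worked cases show the direction of the error:

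1. **Nausea, diary higher.** Intake is minimal for three days, activity is not halved, the participant still works, and there is no extensive or prolonged intervention or repeated prescribed medication. Diary grade 3; below grade 3 under the general rule.
2. **Nausea, diary lower.** Intake is reduced and one day of work is lost. Diary grade 2; grade 3 under the general rule.
3. **Vomiting, diary lower.** Four episodes in a day, some fluid kept down, a day spent in bed. Diary grade 2; grade 3 under the general rule.
4. **Chills, diary lower.** Repeated stronger painkillers without uncontrollable shaking. Appendix 4 grade 3; not clearly grade 3 on the card.
5. **Chills, no change to the endpoint.** Uncontrollable shaking treated by a doctor is diary grade 3. If read as rigors, it is grade 4 in Appendix 4. Both count as grade 3 or above.

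Can a diary entry be regraded to Appendix 4 afterwards? For these symptoms the card collects a grade, free comments and a medication list. The medication list would help with chills. There is no field for bed rest, reduction in activity or lost work, which the general rule needs for nausea and vomiting.

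Which source applies when? In the Section 2.6 schedule, each DNA-C dose is followed by a visit about one week later, and each NYVAC-C dose by one nominally two weeks later. So 3 of 4 immunisations in the DNAx3 group, and 2 of 4 in the DNAx2 group, have a scheduled visit near day 7. Most solicited days in both groups are covered by the diary alone, and the mix of sources is similar but not identical.

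**The case against.** The strongest reply is Section 8.2. If the Clinical Investigators assign the final grade, with review and a route to the Trial Coordinating Committee, the card is only a prompt. Section 7.3 adds that events are validated before analysis, the card calls its table a guide, and participants are asked to contact staff about grade 3 or 4 symptoms. This stands in part, and it rules out saying that the place of recording always decides the grade. It does not settle the matter. Section 4.1.2 says that participants grade, no text links their grade to the investigator's, and the request to call staff is triggered by the card's own grade 3. An event that is grade 2 on the card but grade 3 in Appendix 4 therefore prompts no call. Any later regrading would also be done with the allocation known, since the trial is open to investigators.

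It is also fair to say that the general rule is a stated rule, so the missing rows leave no event ungraded. The difficulty is that the rule disagrees with the card. In case 3, a participant who also reports being in bed all day from fatigue would already count through the malaise row. That limits the effect of that case, but not of cases 1, 2 and 4.

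A reader might infer more than the documents support:

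- **Itching.** The card's row "Itching or irritation in the skin at the site of injection" is graded differently from the irritation wording in Appendix 4. But it is a local reaction, outside the systemic list. The card also records redness in cm and medication taken, from which the Appendix 4 grade can be worked out.
- **Mild rigors becoming grade 4.** Grades 1 and 2 on the card describe no shaking, so this jump does not arise.
- **Triggering the additional committee review.** Section 7.7.1 requires confirmation on attendance or repeat testing, so an unconfirmed diary grade cannot trigger it. The pause rule in Section 7.7.2 does not use the word confirmed, but it does require attribution to a product.
- **A demonstrated shift in the test result.** With 70 per group, 5 v 0 gives a two-sided Fisher p of 2 × (70·69·68·67·66)/(140·139·138·137·136) = 0.058, and 6 v 0 gives 0.028. These counts are hypothetical, and one event near the boundary moves any small-count test.
- **Bias between groups.** Both groups use the same card and receive four immunisations. No material differential error is shown.

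**Conclusion.** The point holds for nausea, vomiting and chills. The protocol names Appendix 4 as the governing scale, gives participants a different one, and does not say how one becomes the other. The two differ at the threshold that defines the primary safety endpoint, in both directions for nausea. Three of the seven systemic components are affected. The number of events that would change class cannot be derived from the document, and investigator review may correct some of them. The conclusion assumes that the general rule is meant to apply to nausea and vomiting, as the opening of Appendix 4 states, and that diary grades enter the analysis on non-visit days, as Section 4.1.2 implies. It should be corrected because the misclassification is avoidable and information not collected on the card cannot reliably be recovered later. It does not undermine the safety comparison as a whole.

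**What to change.** Reconcile Sections 1.5.1, 4.1.2 and 8.2 with Appendices 4 and 5:

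- Add nausea and vomiting rows to Appendix 4, and make the nausea, vomiting and chills/rigors criteria identical in Appendix 4 and on the diary card. The sponsor's clinicians choose the cut-offs; this review takes no view on which criteria are right.
- State that this common scale gives the analysed grade whether an event is recorded in the diary or in clinic, and name who assigns that grade.
- If a criterion based on activity or work is kept, add a field for it to the card.

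The cost is edits to two appendix tables, a sentence on grading responsibility, and a reprinted card.

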#### **4.1.3 Other adverse events**

These will be recorded as reported following an open question to participants, with the

dates of commencement and resolution, and any medication required. They will be graded according to the general principles outlined in appendix 4. Social harm will also be recorded as an adverse event, graded according to the general guidelines.

#### 4.1.4 Routine laboratory and urinary parameters

The following safety assessments will be undertaken in laboratories local to the clinical centre according to standard procedures subject to quality control:

- haematology: haemoglobin, white cell and platelet count, neutrophils and lymphocytes
- chemical pathology: liver function tests (AST/ALT, alkaline phosphatase, bilirubin), creatinine, glucose

Note of clarification 18th April 2008: conjugated bilirubin will take preference over total bilirubin for the purposes of grading hyperbilirubinemia

- immunology CD4 number and percentage  
immunoglobulins A, G and M  
antibodies to DNA and ANA

The following assessment will be undertaken on a specimen of urine, conducted by a member of the study staff according to trial specific standardised operating procedures:

- urinalysis: dipstick conducted by clinical staff and recorded normal/abnormal  
If abnormal a mid-stream urine specimen will be collected in order to grade the event according to appendix 4.

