disorders; uncontrolled infection; autoimmune disease, immunodeficiency or use of immunosuppressives in preceding 3 months

- receipt of live attenuated vaccine within 60 days or other vaccine within 14 days of enrolment
  - receipt of blood products or immunoglobulin within 4 months of screening
  - participation in another trial of a medicinal product, completed less than 30 days prior to enrolment
  - history of severe local or general reaction to vaccination defined as
    - local:** extensive, indurated redness and swelling involving most of the antero-lateral thigh or the major circumference of the arm, not resolving within 72 hours
    - general:** fever  $\geq 39.5^{\circ}\text{C}$  within 48 hours; anaphylaxis; bronchospasm; laryngeal oedema; collapse; convulsions or encephalopathy within 72 hours
  - HIV 1/2 positive or indeterminate on screening
  - positive for hepatitis B surface antigen, hepatitis C antibody or serology indicating active syphilis requiring treatment
  - positive for DNA/ANA antibodies at titre considered clinically relevant by immunology laboratory
  - grade 1 or above routine laboratory parameters (see section 4.1.4 & appendix 4 for definitions).
- Note of clarification 18th April 2008:* hyperbilirubinemia has to be considered as an exclusion criterion only when confirmed to be conjugated bilirubinemia.
- unlikely to comply with protocol

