| Amylase                                         | >1.0 – 1.5 x ULN                                                  | >1.5 – 2.0 x ULN                                                     | >2.0 – 5.0 x ULN                                                   | >5.0 x ULN                               |
| Creatinine                                      | 130-180µmol/l                                                     | 181-360µmol/l                                                        | 361-720µmol/l                                                      | >720µmol/l                               |
| URINALYSIS                               |                                                                   |                                                                      |                                                                    |                                          |
| Proteinuria:
24 hour urine                   | 200 mg - 1 g loss/day
OR <0.3% OR <3 g/l                       | 1 – 2 g loss/day OR
0.3 – 1.0% OR 3 - 10 g/l                      | 2 – 3.5 g loss/day OR
>1.0% OR > 10 g/l                         | Nephrotic syndrome
OR >3.5 g loss/day |
| Haematuria                                      | Microscopic only ≤10 RBC/HPF                                      | >10 RBC/HPF                                                          | Gross, with or without clots OR RBC casts                          | Obstructive OR transfusion req           |

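### Proteinuria is graded from a mid-stream specimen against a table row built on 24-hour losses, and the row's concentration bands can score a grade 3 or 4 daily loss as grade 1 or 2

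*Protocol*

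**What the plan says.** Section 4.1.4 describes the routine urine test as "urinalysis: dipstick conducted by clinical staff and recorded normal/abnormal", so the dipstick itself yields no grade. Grading comes from the next step: "If abnormal a mid-stream urine specimen will be collected in order to grade the event according to appendix 4".

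The proteinuria row of Appendix 4 (Laboratory parameters, Urinalysis) is labelled for 24-hour urine. Each of grades 1 to 3 gives a daily loss first and then two concentration alternatives joined by OR. Grade 1 is "200 mg - 1 g loss/day OR <0.3% OR <3 g/l". Grade 2 is 1 to 2 g/day, or 0.3 to 1.0%, or 3 to 10 g/l. Grade 3 is "2 – 3.5 g loss/day OR >1.0% OR > 10 g/l". Grade 4 is nephrotic syndrome or a loss above 3.5 g/day, with no % or g/l band.

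The grades are then used in several places:
- Section 1.5.1 counts as a primary safety parameter: "Grade 3 or above other clinical or laboratory adverse event confirmed at examination or on repeat testing respectively".
- Section 5.4.1 recommends discontinuation for a confirmed grade 3 or 4 event not resolved within 72 hours.
- Sections 7.7.1 and 7.7.2 trigger committee review, or a halt pending review, when 3 or more participants have qualifying grade 3 or 4 events.
- Section 1.3 excludes volunteers with "grade 1 or above routine laboratory parameters (see section 4.1.4 & appendix 4 for definitions".

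**The concern.** The specimen that section 4.1.4 calls for cannot supply the quantity that leads every quantitative cell of the row. A mid-stream specimen has no collection period, so it cannot show a loss per day. The schedule in 2.6, section 3.1 and section 4.1.4 name no timed collection. That leaves the grader with the % and g/l alternatives, or with nephrotic syndrome at grade 4.

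This would do no harm if the concentration bands were the daily-loss bands in other units. They are not. If they sit much higher, proteinuria that is severe by daily loss is recorded as mild or moderate and can drop out of a primary safety parameter and the monitoring triggers. A repeat test on the same kind of specimen would tend to confirm the lower grade.

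There is a smaller problem at the other end. The daily-loss band for grade 1 starts at 200 mg, while the concentration band beside it has no lower limit.

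**Working it through.** **Inputs from Appendix 4.** Daily-loss cuts: 0.2, 1, 2 and 3.5 g/day. Concentration cuts: 3 and 10 g/l (0.3% and 1.0%).

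**Inputs assumed.** Urine volume V is not stated in the protocol, so I show 1.0, 1.5 and 2.0 l/day. I also take the specimen to be at the day's mean concentration. A single specimen may lie above or below it.

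**Step 1. Are the two concentration scales consistent with each other?** 0.3% is 0.3 g per 100 ml = 3 g/l, and 1.0% = 10 g/l. Yes.

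**Step 2. Which volume would make g/l and g/day agree?** V = daily loss / concentration.
- Grade 1/2 boundary: 1 / 3 = 0.33 l/day.
- Grade 2/3 boundary: 2 / 10 = 0.20 l/day.

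No single volume reconciles the row. This step uses only the row's own figures.

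**Step 3. How does a grade 3 daily loss score on the g/l bands?** Concentration = daily loss / V. On the g/l scale, grade 1 is any loss below 3V g/day and grade 3 needs more than 10V g/day.

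| V (l/day) | 2 g/day as g/l | 3.5 g/day as g/l | Score of the 2 to 3.5 g/day band | Grade 1 below (3V) | Grade 3 above (10V) |
|---|---|---|---|---|---|
| 1.0 | 2.0 | 3.5 | grade 1 below 3 g/day, grade 2 from 3 g/day | 3.0 g/day | 10 g/day |
| 1.5 | 1.33 | 2.33 | all grade 1 | 4.5 g/day | 15 g/day |
| 2.0 | 1.0 | 1.75 | all grade 1 | 6.0 g/day | 20 g/day |

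**Step 4. How far does this depend on V?**
- The bottom of the grade 3 band scores grade 1 once V exceeds 2 / 3 = 0.67 l/day.
- The whole band scores grade 1 once V exceeds 3.5 / 3 = 1.17 l/day.
- Even the top of the band exceeds 10 g/l, and so scores grade 3, only if V is below 3.5 / 10 = 0.35 l/day.

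**Step 5. How does a grade 4 daily loss (above 3.5 g/day) score?**
- V = 1.0 l: none scores grade 1. Losses up to 10 g/day score grade 2, and larger ones grade 3.
- V = 1.5 l: below 4.5 g/day scores grade 1, 4.5 to 15 scores grade 2, and above that grade 3.
- V = 2.0 l: below 6 g/day scores grade 1, 6 to 20 scores grade 2, and above that grade 3.

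No g/l value gives grade 4. From this specimen, grade 4 is reached only through the label of nephrotic syndrome.

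**Step 6. The low end.** The floor "200 mg - 1 g loss/day" corresponds to 0.2 / V = 0.2 g/l at 1.0 l and 0.1 g/l at 2.0 l. The alternative "OR <0.3% OR <3 g/l" has no floor, so any protein concentration found after an abnormal dipstick meets grade 1.

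**The case against.** The strongest objection is that the protocol leaves room for better information. Section 4.3.4 allows other clinically indicated assessments after an adverse event. Section 5.4 promises operating procedures for abnormal urinalysis. Sections 3.1 and 4.1.4 refer to trial-specific procedures that are not shown. Sections 7.6 and 8.2 provide for committee review of grades. The bands are joined by OR, so a daily loss would count if someone measured it. All of this stands, and it softens the consequence. It does not remove the conflict, because none of these places names another specimen for grading, while section 4.1.4 names one.

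A reader might infer that any grade 3 or 4 proteinuria will be scored as grade 1. The figures do not support that. At 1.0 l/day part of the grade 3 band scores grade 2. Grade 4 has no upper end, so its losses can score 1, 2 or 3. Volume and the representativeness of the specimen are assumptions.

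A reader might also infer that severe proteinuria would be missed in the endpoint, the discontinuation decision and the halting rule alike. That goes too far. Discontinuation is at the investigator's discretion under 5.4.1, the nephrotic syndrome route stays open, and 7.7.2 needs 3 or more participants with events attributed to the same product.

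The screening consequence is arguable. Section 1.3 speaks of routine laboratory parameters, and the heading of 4.1.4 separates those from urinary ones. Against that, 1.3 cites both 4.1.4 and Appendix 4, and Appendix 4 lists urinalysis among the laboratory parameters.

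The mid-stream specimen is not a mistake in itself, since it can serve the haematuria row, which counts cells per field. Both arms are graded in the same way, so no bias between arms is shown. Participants are screened healthy volunteers, and the protocol gives no expected number of such events.

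**Conclusion.** The concern holds in a limited form. The specimen conflict between 4.1.4 and the Appendix 4 row, and the mismatch between its g/l and g/day bands (implied volumes 0.33 and 0.20 l/day), follow from the document alone. The size of the under-grading rests on two assumptions: 1 to 2 l of urine a day, and a specimen at the day's mean concentration. Under these, every loss in the 2 to 3.5 g/day band scores grade 1 or 2, and a loss above 3.5 g/day scores grade 1 or 2 unless its concentration exceeds 10 g/l. Either score is below the grade 3 threshold in 1.5.1, 5.4.1, 7.7.1 and 7.7.2, so such events can be lost from those counts unless a further assessment or the nephrotic syndrome label brings them back. How many events this touches cannot be derived from the protocol. The missing floor at grade 1 matters only if the exclusion in 1.3 covers urinalysis, which the protocol should make clear. The point is worth correcting because it reaches a primary safety parameter and is cheap to repair.

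**What to change.** Reconcile section 4.1.4 with the proteinuria row of Appendix 4 so that the specimen collected and the bands applied measure the same thing across grades 1 to 4. One way is a volume-independent measure, such as a protein:creatinine ratio, on the mid-stream specimen already collected, with one set of bands that includes grade 4. Another is to keep the daily-loss bands alone and name a timed collection after a confirmed abnormal dipstick, which adds a procedure for participants. In either case give grade 1 a lower limit, state whether the exclusion in 1.3 applies to urinalysis, and keep the mid-stream specimen for haematuria. The cut-points are for the safety group to set.

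The change is one table row, one sentence in 4.1.4 and a clarification in 1.3. The downside is that some events may be graded higher than under the present text.
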